## Abstract

Transcranial direct current stimulation (tDCS) has become established as an effective therapeutic approach, employed to modulate cortical excitability in various conditions. Nonetheless, few studies have assessed the use of tDCS in improving respiratory performance both in healthy and in subjects with respiratory disfunction. This randomized double-blind placebo-controlled trial evaluated the outcomes of lung function, strength of inspiratory muscles, general strength after intervention with bilateral tDCS both in young and elderly female subjects. Eighty subjects were randomized into four groups divided by age (40 young and 40 elderly) and intervention vs. placebo. After a basal (day 1) evaluation all subjects performed two evaluation/intervention rounds with 48 to 72 h interval. Lung function evaluated with spirometry evaluation with Forced vital capacity (FVC), Forced Expiratory Volume in 1 S (FEV_1_), FEV_1_/FVC Ratio, Maximal Voluntary Ventilation (MVV); Dynamic Inspiratory muscle strength evaluated with Powerbreathe and general strength with dynamometer. This study intends to understand the behavior of respiratory muscle strength and endurance after intervention with bilateral cathodal tDCS over the primary motor cortex in healthy young and elderly subjects, as a bridge for larger studies both in healthy and rehabilitation setting.

Specifications table

**Table utbl0001:** 

Subject area:	Neuroscience
More specific subject area:	Effects of bilateral cathodal tDCS application in muscle strength and pulmonary performance in the young and elderly population.
Name of your protocol:	Bilateral transcranial direct-current stimulation on muscle strength and respiratory endurance: randomized, placebo-controlled, double-blind trial protocol
Reagents/tools:	Bilateral tDCS: Neuromodulator from Microestim Foco Research, NKL, Santa Catarina, Brazil. Forced vital capacity (FVC), Forced Expiratory Volume in 1 S (FEV1), FEV1/FVC Ratio, Maximal Voluntary Ventilation (MVV): SPM-A spirometer CONTEC™, China Powerbreathe K5 equipment (Powerbreathe, Southam, England): S-INDEX, Flow and Volume. Handgrip strength: hydraulic dynamometer (Saehan, Beijing, China).
Experimental design:	Randomized placebo-controlled double-blind trial. Four groups (*n* = 68), test (young and elderly, *n* = 34) and placebo (young and elderly, *n* = 34). Outcome measures were evaluation of lung function, strength of inspiratory muscles, general strength. After a basal evaluation, the outcomes were tested in two separated moments before and after bilateral cathodal tDCS stimulation both comparing in the same age group and comparing elderly versus young.
Trial registration:	U1111–1310–2605, International Clinical Trial Registry Platform
Ethics:	The study was conducted in line with recommendations from the Declaration of Helsinki and received ethical approval from the Ethics Committee of the Federal University of the Amazonas, Brazil [CAAE66350622.0.0000.520, evaluation 315.763].
Value of the Protocol:	tDCS is proven to be a valuable tool in rehabilitation and performance enhancement in several areas, but with little or no work done in respiratory function or respiratory rehabilitation. The main objective is to evaluate the expected improvement of the respiratory muscle strength and resistance after intervention with bilateral tDCS over the primary motor cortex in healthy young and elderly subjects. It is a randomized, double-blinded study designed to study the possibility of using tDCS for enhance respiratory performance in healthy subjects or in rehabilitation programs after respiratory injury. We highlight the construction of the study, allowing the comparison between the response in the young and the elderly.

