### Research questions

-Compared to controls, is cathodic bilateral tDCS stimulation effective in improving muscle strength and respiratory performance?-Will there be a change in the effects of cathodic bilateral tDCS when performed in the young vs. elderly regarding muscle strength gain/better respiratory performance?

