### Sample size and subject recruitment

The volunteers were recruited after posting invitation posters on the campus of the Federal University of Amazonas. No compensation was offered for participation in the experiment. All the subjects were female. The rationale for this was the ease of recruiting female participants, since there are activities taking place on the university campus only for elderly female.

Were inclusion criteria for the young group – ages comprehended between 18 and 25, no medical history of cardiovascular, pulmonary or neurologic conditions affecting the respiratory tract. Regarding the elderly group the inclusion criteria were the same, except the timeframe, considering ages between 60 and 80 years of age. Exclusion criteria were subjects out of the timeframe requested by the study protocol in both groups, medical history of cardiovascular, pulmonary or neurologic conditions. Also, in the selection of volunteers for the young group, those who were at the time of their menstrual period were excluded to avoid any hormonal influence on the results.

For the sample size, inspiratory muscle strength will be used through the dynamic inspiratory pressure (*S index*). As there is no study that evaluated this type of variable associated with tDCS, we will accept a priori a Cohen's size effect *F* = 0.25 (Small Effects). For sample size, ANOVA two-way repeated measures (Between-within) was calculated. Parameters used were size effect 0.25, α = 0.05, β = 80 %, 2 groups, 2 measurements (tDCS stimuli and Sham stimuli), correction between measurements = 0.5 and correction of no-sphericity ε = 1. Accepting a possible 20 % of sample loss, a sample calculation of 40 volunteers was selected both for the elderly and young group, with a global total of 80 subjects and G power 3.1 (University of Dusseldorf, Dusseldorf, Germany) was used for calculation.

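### The sample-size calculation covers active versus sham within one age group, not the highlighted young-versus-elderly comparison, which should be estimated with a confidence interval and labelled exploratory

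*Protocol article*

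**What the plan says.** Under Research questions, the article asks two things. The first is whether stimulation improves strength and respiratory performance against control. The second begins "Will there be a change in the effects of cathodic bilateral tDCS when performed in the young vs. elderly". The Specifications table lists the elderly-versus-young comparison in its design row, and in its value row it adds "We highlight the construction of the study, allowing the comparison between the response in the young and the elderly".

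Sample size and subject recruitment contains one calculation. The endpoint is the S-index ("inspiratory muscle strength will be used through the dynamic inspiratory pressure") and the model is given as "ANOVA two-way repeated measures (Between-within) was calculated". The inputs are "Parameters used were size effect 0.25, α = 0.05, β = 80 %, 2 groups, 2 measurements", with a correlation of 0.5 and no sphericity correction. After a 20% allowance for loss, 40 subjects are taken for each age group, 80 in all. They are randomized as four groups of 20. The Specifications table instead gives 68, with 34 test and 34 placebo.

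Statistical analysis names a two-way between-within ANOVA with Bonferroni post hoc tests for evaluating the intervention, judged at p < 0.05. No passage attaches a power to the age comparison or calls it exploratory.

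**The concern.** Whether the tDCS effect differs by age is a question about a difference between two active-versus-sham effects. With equal cells, its estimate has twice the variance of either effect alone. A calculation that just gives adequate power for one effect therefore gives clearly less for the difference between two of the same size.

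The planned analysis adds to this. A two-way between-within ANOVA has one between-subject factor and time. Run separately by age, it contains no age contrast. Run with the four groups as a single factor, its group-by-time test has three degrees of freedom and mixes age, arm and their combination. Pairwise post hoc tests do not supply the missing contrast either, because they compare cells and not effects.

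At stake is the answer to question 2. If tDCS worked at one age and not at the other, a non-significant result would still be quite likely. Without an interval, it could be taken as a similar response at both ages and carried into the larger studies for which the abstract calls this trial a bridge.

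**Working it through.** **Inputs** (all from Sample size and subject recruitment): f = 0.25, α = 0.05, power 80% (printed as β), 2 groups, m = 2 measurements, ρ = 0.5 ("correction between measurements = 0.5"), ε = 1. Cell sizes are 20 as randomized (80 in four groups), or 17 from the 68 in the Specifications table (68/4).

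**Step 1: reproduce the plan's figure.** For the group-by-time interaction, λ = f²·N·m/(1−ρ) with F(1, N−2).
- N = 34: λ = 0.0625 × 34 × 2/0.5 = 8.5, power 80.7%. N = 32 gives 78.1%, so 34 is the smallest even number that reaches 80%.
- Adding 20%: 34 × 1.2 = 40.8, in line with the stated 40. At N = 40, power is 86.9%.
- 2 × 34 = 68 and 2 × 40 = 80, the two totals in the article.

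**Step 2: check which contrast was sized.** The article words the inputs as "2 groups, 2 measurements (tDCS stimuli and Sham stimuli", which does not fit parallel arms, so other readings were tried. If the two groups were young and elderly, 34 would be the total for the trial and not the number per age group. A between-group main effect would need 98, and a four-group interaction 48. Only active versus sham within one age group, done once per age group, gives 68 and 80.

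**Step 3: express the planned effect in SDs of change.** With ρ = 0.5, the SD of change is σ√(2(1−ρ)) = σ. For a difference δ in mean change with n per arm, λ = δ²·n/2. Setting 8.5 = δ² × 17/2 gives δ = 1.0 SD of change.

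**Step 4: the age contrast.** Let Δ = (active − sham change in the elderly) − (active − sham change in the young), in SDs of change. Four cells of n give SE = √(4/n), so λ = Δ²·n/4 with F(1, 4n−4).
- n = 17: SE = 0.485. At Δ = 1.0, λ = 17/4 = 4.25.
- n = 20: SE = 0.447. At Δ = 1.0, λ = 20/4 = 5.0.

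| Age difference Δ (SD of change) | Power, 17 per cell | Power, 20 per cell |
|---|---|---|
| 0.5 | 17.4% | 19.7% |
| 0.75 | 33.1% | 38.1% |
| 1.0 (full effect at one age, none at the other) | 52.8% | 59.8% |
| 1.5 | 86.1% | 91.2% |
| 2.0 | 98.2% | 99.3% |

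A simulation of the Δ = 1.0 row gave 52.9% and 60.2%.

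**Step 5: precision.**
- Δ detectable with 80% power: 1.38 (n = 17) or 1.27 (n = 20).
- 95% CI half-width, t × SE: 0.97 (n = 17) or 0.89 (n = 20).
- 80% power at Δ = 1.0 would need 128 evaluable subjects (32 per cell), against 68 to 80 planned.

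**The case against.** The strongest reply is that nothing stated is wrong. The calculation reproduces, and the article ties the 40 to each age group. Saying that the design allows the age comparison is true as a statement about structure, since sham is present at both ages. The main objective and the primary outcome concern improvement and test versus sham, and sizing a trial on its main contrast is ordinary practice. Power for a further comparison can also be left to an analysis plan that is not shown. All of this stands. It rules out calling the point an arithmetic error, and low power alone would not justify a comment.

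Two further replies limit the figures.
- The 53% to 60% might be read as a ceiling. It is not one: it assumes that Δ is no larger than the planned effect. The Background and the cited work allow for both excitation and inhibition, so opposite responses at the two ages are not excluded, and a Δ of 1.27 to 1.38 SD would reach 80%. Entering f = 0.25 for the age term itself gives 98% to 99%, but that means Δ = 2.0 SD, twice the planned effect, which the article does not propose.
- Comparing only the stimulated young with the stimulated elderly has 81% to 87% power at f = 0.25. It drops the sham arms, however, and so does not answer a question about the effect of stimulation against control.

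What the objection leaves untouched is the analysis. The age difference is one of two research questions and a highlighted feature, and the ANOVA named for evaluating the intervention does not isolate it.

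**Conclusion.** The point holds as a mismatch of scope. The 80% applies to active versus sham within one age group, where it is correct. It does not extend to question 2. On the plan's own inputs, with equal cells, a common SD of change and an age difference equal to the whole planned effect, power is about 53% (17 per cell) to 60% (20 per cell). The 95% CI would extend about 0.9 to 1.0 SD of change on either side, so an estimate of zero would barely exclude an age difference as large as the full planned effect.

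A reader might infer that the protocol claims 80% power for the age comparison, or that it intends to report no age difference when p ≥ 0.05. It says neither. What can be improved is how question 2 is estimated, labelled and interpreted.

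**What to change.** 1. For question 2, estimate the age × arm × time contrast directly: active-minus-sham change in the elderly minus active-minus-sham change in the young, with its 95% CI. Use this in place of the p-value from the two-way ANOVA.
2. Label the age comparison exploratory.
3. Say in the sample-size section that the 80% applies to active versus sham within an age group.
4. State that p ≥ 0.05 for the age contrast will not be read as an equal response in young and elderly.

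The cost is a few sentences and one contrast computed from data already being collected. No extra subjects are needed. The downside is a less favourable statement about the comparison that the article highlights. Data analysis is described as ongoing, so the contrast should be declared before the age results are looked at, or reported as a later addition.

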## Background

Transcranial direct current stimulation (tDCS) has become established as an effective therapeutic approach, employed to modulate cortical excitability in various conditions, including depression or post-stroke rehabilitation. It involves the placement of two or more electrodes on the scalp, delivering a 1–2 mA current to a specific cortical region [1]. The rapid effects of low intensity neurostimulation alters action potential leading to depolarization or hyperpolarization [2,3]. While tDCS, particularly applied to the primary motor cortex (M1), has prompted investigation into its potential for improving motor function in both healthy subjects and various conditions with the expectation that it facilitates neuroplasticity and brain functional/structural reorganization. This is achieved through the modification of synaptic bindings by inductive long-term potentiation and long-term depression, as well as the modulation of neuronal resting membrane potential [[4], [5], [6]]. The assembly of the tDCS can be done unilaterally or bilaterally, and with anodic or cathodic stimulation. Interestingly, cathodal stimulation can have different effects depending on the current intensity. Studies have shown that 2.0 mA has an excitatory effect, while intensities of 1.0 mA and 3.0 mA seem to cause inhibition of the cerebral cortex [[7], [8], [9], [10], [11]]. A recent meta-analysis showed bilateral tDCS was more effective to improve motor performance in healthy individuals, while unilateral tDCS was stronger in rehabilitation of pathological conditions such as stroke [12].

Voluntary control of breathing involves the M1 cortex and premotor region, adding a major cortical component activated during exercise, speech, or voluntary respiratory maneuvers [[13], [14], [15]]. Nevertheless, other mechanisms participate in this control, such as pH or pCO_2_ [16]. Few studies have assessed the use of tDCS in improving respiratory performance both in healthy and in subjects with respiratory disfunction. De Carvalho et al., [17] evaluated two patients with spinal cord injury who were having difficulty weaning off tracheostomy. The authors demonstrated a slight increase in respiratory muscle strength in both patients. Andrade et al., [18] performed unilateral tDCS targeting the motor area of the diaphragm on the left side in patients in the intensive care unit with COVID-19. They showed that patients who received stimulation combined with physiotherapy had a shorter length of stay. However, no assessment of respiratory function values was conducted. On the other hand, Azabou et al., [16] demonstrated that unilateral tDCS can decrease the excitability of the corticospinal pathway of the ventilatory motor system, particularly the diaphragmatic function. Despite some studies failing to confirm the real impact of tDCS on respiratory function, others demonstrate decreased corticospinal excitability over the motor respiratory pathway, increased muscle consistency, and heightened activity when applied to the spinal motor area. However, to date, no study has assessed the effects of bilateral tDCS in motor areas and the impacts on the strength and resistance of respiratory muscles

### Research questions

-Compared to controls, is cathodic bilateral tDCS stimulation effective in improving muscle strength and respiratory performance?-Will there be a change in the effects of cathodic bilateral tDCS when performed in the young vs. elderly regarding muscle strength gain/better respiratory performance?

## Description of protocol

Methods details

### Ethical approval

The study was conducted in line with recommendations from the Declaration of Helsinki and received ethical approval from the IRB of the Federal University of the Amazonas, Brazil [CAAE66350622.0.0000.520].

### Sample size and subject recruitment

The volunteers were recruited after posting invitation posters on the campus of the Federal University of Amazonas. No compensation was offered for participation in the experiment. All the subjects were female. The rationale for this was the ease of recruiting female participants, since there are activities taking place on the university campus only for elderly female.

Were inclusion criteria for the young group – ages comprehended between 18 and 25, no medical history of cardiovascular, pulmonary or neurologic conditions affecting the respiratory tract. Regarding the elderly group the inclusion criteria were the same, except the timeframe, considering ages between 60 and 80 years of age. Exclusion criteria were subjects out of the timeframe requested by the study protocol in both groups, medical history of cardiovascular, pulmonary or neurologic conditions. Also, in the selection of volunteers for the young group, those who were at the time of their menstrual period were excluded to avoid any hormonal influence on the results.

For the sample size, inspiratory muscle strength will be used through the dynamic inspiratory pressure (*S index*). As there is no study that evaluated this type of variable associated with tDCS, we will accept a priori a Cohen's size effect *F* = 0.25 (Small Effects). For sample size, ANOVA two-way repeated measures (Between-within) was calculated. Parameters used were size effect 0.25, α = 0.05, β = 80 %, 2 groups, 2 measurements (tDCS stimuli and Sham stimuli), correction between measurements = 0.5 and correction of no-sphericity ε = 1. Accepting a possible 20 % of sample loss, a sample calculation of 40 volunteers was selected both for the elderly and young group, with a global total of 80 subjects and G power 3.1 (University of Dusseldorf, Dusseldorf, Germany) was used for calculation.

The stratification randomization (age, BMI, FVE1 and FVC) was electronically conducted by an investigator that did not take part in the evaluation of patients of application of the tests. Electronic codes were generated to introduce in the tDCS neuromodulator ensuring the blinding of the therapist and the subject assessed (doble blind). The volunteers of this research will be randomized in four groups: 20 volunteers per group, being 20 for young interventional and young placebo, and the same for the elderly. After a basal (day 1) evaluation all subjects will be part of two evaluation/intervention rounds with 48 to 72 h interval (Fig. 1).

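### The sample size is labelled as covering a small effect, but in the parallel active/sham, pre/post design f = 0.25 is a 1.0 SD between-arm difference in change, and the repeated factor is misnamed

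*Protocol article*

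**What the plan says.** Under Sample size and subject recruitment, the Protocol article bases the calculation on the S-Index. The effect size is "size effect *F* = 0.25 (Small Effects", and the article explains that this value is a convention: "As there is no study that evaluated this type of variable associated with tDCS, we will accept a priori". The test is given as "ANOVA two-way repeated measures (Between-within) was calculated", with "α = 0.05, β = 80 %, 2 groups, 2 measurements (tDCS stimuli and Sham stimuli" and "correction between measurements = 0.5 and correction of no-sphericity ε = 1". The result is 40 per age group: "Accepting a possible 20 % of sample loss, a sample calculation of 40 volunteers was selected both for the elderly and young group", 80 in total. The Specifications table gives 68 across four groups.

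The next paragraph randomises volunteers to four groups of 20, active or placebo within each age group. The section on tDCS placement says the sham group receives no electrical stimulation. The Day 2, post-intervention and Day 3 descriptions have every participant tested before and after stimulation on each stimulation day.

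**The concern.** Two statements in the sample size paragraph do not fit the trial described around it.

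- **The label.** f is not a standardised mean difference. In a two-by-two between-within interaction, a value of f that looks modest corresponds to a difference in change four times as large in SD units. Calling 0.25 small tells the reader that the trial has 80% power for small effects.
- **The repeated factor.** The two measurements are given as active and sham stimulation. No participant receives both. Arm is the between-subject factor, and the repeated factor is pre/post. As worded, the calculation describes a crossover.

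At stake is how the S-Index result is read. The article presents the trial as a step towards larger studies, so a non-significant result judged against a claimed 80% power for small effects would carry more negative weight than the design supports.

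**Working it through.** **Inputs** (all from Sample size and subject recruitment): f = 0.25, α = 0.05, power 80% (written as β), k = 2 groups, m = 2 measurements, ρ = 0.5, ε = 1. Allocation is 1:1 within each age group.

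**1. Reproduce the plan's figure.** For the within-between interaction the noncentrality is λ = f² × N × m / (1 − ρ), with df1 = (k − 1)(m − 1) = 1 and df2 = (N − k)(m − 1) = N − 2.

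- N = 34: λ = 0.0625 × 34 × 2 / 0.5 = 8.5, df (1, 32), power 80.7%.
- N = 32: λ = 8.0, power 78.1%.

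So N = 34 per age group, and 2 × 34 = 68 matches the Specifications table. Adding 20% gives 34 × 1.2 = 40.8, close to the stated 40.

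**2. Which effect does f = 0.25 describe?** N = 34 alone does not settle this. The within-subject main effect has the same λ and error degrees of freedom, so it also gives 34; there f = 0.25 would be a 0.5 SD mean difference. The design settles it: with parallel active and sham arms tested before and after, the treatment effect is the arm-by-time interaction.

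**3. Convert f to a difference in change.** In a two-by-two interaction, f = 0.25 places each cell 0.25 SD from its additive value. The between-arm difference in change is Δ = 4 × 0.25 SD = 1.0 SD of a single measurement. The SD of change is SD × √(2(1 − ρ)) = SD × √(2 × 0.5) = SD, so Δ is also 1.0 SD of change.

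Check: a two-sample t test on change with d = 1.0 and 17 per arm has squared noncentrality 1.0² × 17/2 = 8.5 and power 80.7%, the same test. A simulation gave 80.6%.

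**4. Power at smaller differences**, ρ = 0.5:

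| Difference in change | f | 34 evaluable | 40 evaluable |
|---|---|---|---|
| 1.0 SD | 0.25 | 80.7% | 86.9% |
| 0.8 SD | 0.20 | 61.9% | 69.3% |
| 0.5 SD | 0.125 | 29.3% | 33.8% |
| 0.4 SD | 0.10 | 20.5% | 23.4% |
| 0.2 SD | 0.05 | 8.7% | 9.5% |

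At f = 0.10, 80% power needs N = 200 per age group (λ = 0.01 × 200 × 2 / 0.5 = 8.0, power 80.4%).

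**5. Sensitivity at f = 0.10.** Pooling the two age groups at ρ = 0.5 gives 36.9% at 68 evaluable and 42.4% at 80. Keeping 34 per age group and raising ρ to 0.7, 0.8 or 0.9 gives 31%, 43% or 72%.

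**6. Precision.** The expected 95% CI half-width for the difference in change at ρ = 0.5 is t × √(2/n) in SD units: 2.037 × √(2/17) = 0.70 SD at 17 per arm, and 2.024 × √(2/20) = 0.64 SD at 20 per arm.

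**The case against.** The strongest reply is that nothing was miscalculated. The article prints every input, the 80% claim is attached to f = 0.25, and at f = 0.25 it is correct. On this view only a parenthesis is wrong. That stands as far as N is concerned: a reader might infer that the sample size is an arithmetic error, and it is not.

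Three further objections have force.

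- **The value of small is assumed.** A reader might take 20% as the trial's true power for a small effect. The article gives no value for small other than 0.25, so f = 0.10 is an assumption, and the figure moves with it.
- **The correlation is a planning value.** Pre and post tests are taken in the same session under the same conditions, so ρ above 0.5 is plausible. The half-width at 17 per arm would then fall to 0.54, 0.44 or 0.31 SD at ρ = 0.7, 0.8 or 0.9. Pooling both ages and taking ρ = 0.9 together would exceed 80% at f = 0.10 (λ = 0.01 × 68 × 2 / 0.1 = 13.6, power 95%). The article sizes each age group separately at ρ = 0.5, so that combination is not its basis.
- **Power is not exclusion.** A reader might infer that a null result could exclude nothing below 1.0 SD. With a half-width of about 0.70 SD, an estimate near zero would exclude 0.8 SD.

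The article also never says that a null result would rule out small effects; that is a risk of misreading. What the reply does not remove is that the label and the named measurements are both wrong for the design described.

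**Conclusion.** Wrong as written, and correctable by wording. For the active/sham by pre/post comparison at ρ = 0.5, the trial has about 80% power within each age group for a 1.0 SD between-arm difference in change. That is a large difference, and the conversion follows from the article's own settings. N = 34 per age group is reproduced and is not in dispute.

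The shortfall for a small effect depends on what small means. If it is f = 0.10, power per age group is about 20% to 23% at ρ = 0.5; if it is a 0.2 SD difference, about 9%. Pooling ages alone, or raising the correlation as far as 0.9 alone with 34 evaluable, still leaves power at f = 0.10 below 80%.

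The 1.0 SD reading rests on the randomised design, because N = 34 would also come from a within-subject main effect. A reader might infer from the named measurements that a crossover was intended; the randomisation paragraph and the description of the sham group do not support that.

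**What to change.** In Sample size and subject recruitment:

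- Delete the small-effects label.
- State that, within each age group, 34 evaluable participants (17 per arm) give about 80% power for a 1.0 SD between-arm difference in pre-to-post S-Index change, assuming a correlation of 0.5, and that power is lower for smaller differences (about 62% at 0.8 SD and 29% at 0.5 SD).
- Name the two groups as active and sham, and the two measurements as pre and post.
- Replace β = 80% with power = 80%.

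Report the between-arm difference in change with its 95% CI, noting an expected half-width of about 0.70 SD at 17 per arm or 0.64 SD at 20 per arm when the correlation is 0.5. Do not add a statement that effects below 1.0 SD cannot be excluded; the interval decides that.

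Cost: wording only. N, allocation and the planned ANOVA are unchanged, and no participants are added. The downside is that the stated capability becomes less favourable.

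### The sample-size paragraph labels 80% as β when the figure used was evidently power (1 − β) = 80%: a minor mislabelling, not a plan for 20% power

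*Protocol article*

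**What the plan says.** The sample-size paragraph (Protocol article, Sample size and subject recruitment) bases the calculation on the S-index. It names the model: "ANOVA two-way repeated measures (Between-within) was calculated". The inputs follow: "Parameters used were size effect 0.25", then "α = 0.05, β = 80 %, 2 groups, 2 measurements", then "correction between measurements = 0.5 and correction of no-sphericity ε = 1". The two measurements are described in this way: "2 groups, 2 measurements (tDCS stimuli and Sham stimuli". The allowance for attrition is "Accepting a possible 20 % of sample loss", and the result is "a sample calculation of 40 volunteers was selected both for the elderly and young group, with a global total of 80 subjects". The number required before the allowance is not given there.

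The specifications table gives a total of 68, as 34 test and 34 placebo. The randomization paragraph gives four cells of 20. No other section states a power or a type II error; the remaining mentions of G power are the name of the software.

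**The concern.** Set beside α, a type I error rate, β is read as the type II error rate. Taken at its word, the paragraph accepts an 80% chance of missing the planned effect. This is the operative justification of the sample size, and the article says under Protocol validation that data analysis is under way. The planned false-negative rate is part of how readers will interpret a null result on the S-index, and it is printed at four times the value that fits the sample size (80% against 20%). Because it is the only such statement, a reader has to infer the intended figure from the sample size itself.

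**Working it through.** **Inputs**, all from the sample-size paragraph: f = 0.25, α = 0.05, k = 2 groups, m = 2 measurements, ε = 1, 20% loss, 40 per age group. The 0.5 is printed as "correction between measurements = 0.5". I read it as ρ, the correlation among repeated measures, which is the quantity this model needs.

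**Formula.** For the group-by-measurement interaction, power comes from the noncentral F distribution with

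- λ = f² · N · m · ε / (1 − ρ) = 0.0625 · N · 2 · 1 / 0.5 = 0.25 N
- df1 = (k − 1)(m − 1) = 1
- df2 = (N − k)(m − 1) = N − 2

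where N is the number in one age group.

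| N per age group | Power |
|---|---|
| 6 | 0.159 |
| 8 | 0.223 |
| 32 | 0.781 |
| 33 | 0.795 |
| 34 | 0.807 |
| 40 | 0.869 |

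**The plan's own figure, with 80% read as power.** The smallest N that reaches 0.80 is 34. Two age groups give 2 × 34 = 68, the total in the specifications table. Adding 20% gives 34 × 1.2 = 40.8, which is close to the 40 chosen.

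**The text as printed, with β = 0.80 and so power 0.20.** With equal arms the smallest N is 8 (power 0.223), or 8 / 0.8 = 10 after the loss allowance. Other readings at 20% power do not reach 40 either: the between-group main effect needs 18 per age group (22 or 23 after loss), α = 0.10 needs 6 (8 after loss), and four groups need 16 in total.

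**Which effect gives 34.** At 80% power the interaction and the within-subject main effect both need 34, because with k = m = 2 they share λ and degrees of freedom. The between-group main effect would need 98. So 34 belongs to a within-subject contrast, and the text should say which one.

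**Loss allowance.**

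- To keep 34 after 20% loss: 34 / (1 − 0.20) = 42.5, so 43.
- Loss that 40 can absorb: 1 − 34/40 = 0.15.
- Number left from 40 after 20% loss: 40 × 0.80 = 32, with power 0.781.

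**The case against.** The strongest reply is that no reader familiar with power calculations would be misled. An 80% printed among G*Power inputs that end at 40 per age group can hardly mean anything except power, and the specifications table supports this with 68. Most of that stands. The intent can be recovered, the computation used the conventional value, and only the symbol is wrong.

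Three stronger readings are therefore not supported:

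- *The trial was planned at 20% power, or is too small.* The inputs give 8 per age group at 20% power and the article enrols 40, where power for f = 0.25 under the stated model is 0.87.
- *The calculation cannot be reproduced.* It can be, to 34, once the 80% is read as power and the 0.5 as a correlation. Only the literal symbol blocks it.
- *A null result is expected four times in five even if the effect is real.* That follows from the printed symbol, not from any trial that was planned.

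Two qualifications limit the reply. The specifications table attaches 34 to test and to placebo, not to each age group, and does not call 68 the number before loss, so it corroborates the intended power without stating it. Also, correcting β does not by itself give exactly 40: the two usual ways of adding 20% give 40.8 and 42.5.

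A further objection is that printing 0.807 could give false assurance. The paragraph identifies the two measurements as active and sham stimulation, whereas the randomization paragraph and the section on tDCS placement make these separate parallel groups. This stands: the power figures hold only for a two-measurement interaction, so the fix must identify the measurements.

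**Conclusion.** The point holds as a mislabelled error rate, of minor severity. The printed type II error is 80%, and the value consistent with the sample size is 20%. The required number per age group is 8 under the first and 34 under the second. Power for f = 0.25 is 0.807 at 34, 0.87 at 40, and about 0.78 at the 32 left after the stated 20% loss, so the shortfall against 80% at the planned attrition is about 2 percentage points.

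These figures rest on reading 0.5 as the correlation among repeated measures, on the group-by-measurement interaction as the target effect, and on two within-subject measurements (for example before and after stimulation on one day) compared between the parallel active and sham groups. That 34 is the figure behind 40 is an inference. It fits the 68 in the specifications table, but the sample-size paragraph does not state it.

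**What to change.** In the sample-size paragraph:

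1. Replace the β entry with power (1 − β) = 80% (β = 20%). In the same sentence, call the 0.5 the correlation among repeated measures; this second change is wording only.
2. State the number required before loss, 34 per age group (power 0.807), and that the calculation is for the group-by-measurement interaction. Identify the two measurements in a way that agrees with active and sham stimulation being parallel groups.
3. Report that 40 per age group covers about 15% loss from 34, and that after 20% loss 32 remain, with power about 0.78 for f = 0.25.

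The cost is a few sentences. Enrolment and analysis do not change.
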